#### Recurrent stroke prediction

##### Sample size

For this study, a prediction model containing a maximum of six predictors will be developed for recurrent stroke. Therefore, at least 60 patients with a recurrent stroke are needed according to statistical guidelines.^35^ Ischemic stroke is estimated to recur in approximately 10% of the included patients.^36^ When accounting for a loss to follow-up rate of 10%, the required sample size will be approximately 650. Based on a historical stroke cohort (Dutch Acute Stroke Study: 2009–2013, METC number 08–373), we expect a participation rate of 90%.^37^ Thus, a minimum of 720 patients need to be asked for study participation. In a period of 36 months, at least 720 patients with suspected ischemic stroke will visit the Amsterdam UMC—location AMC, the St. Antonius hospital—location Nieuwegein and the UMC Utrecht.

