The two-year recurrence rate has been estimated to be 12% in patients with AIS.^24^ Clinical prediction models have been developed for predicting recurrence, but heterogeneity is high.^25^ CT-derived predictors have been identified as prognostic for clinical outcome after AIS, but not yet for recurrences.^14^ The second goal of ENCLOSE is to prospectively evaluate the added value of CT-derived predictors for predicting recurrent ischemic stroke. If applicable, MRI-derived predictors will be evaluated additionally.

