## Methods/design

### Study design

ENCLOSE (ClinicalTrials.gov Identifier: NCT04019483) is a prospective multicenter observational cohort study, which will be conducted in three Dutch stroke centers: the University Medical Center (UMC) Utrecht, the Amsterdam UMC—location Academic Medical Center (AMC) and the St. Antonius Hospital—location Nieuwegein. Patient selection, study procedures, and outcome evaluations are described in Figure 1. We will include 720 patients with suspected AIS. At presentation, patients undergo clinical evaluation, laboratory testing, and CT imaging according to local stroke protocols. The local imaging protocol for stroke includes NCCT, CTP, and CTA. Two centers will perform non-ECG-triggered CTA from the base of the heart up to the top of the head; one center will perform a non-ECG-triggered CTA from the aortic arch to the head and a separate ECG-triggered cardiac CTA. Patients with a suspected small volume infarct will be asked to undergo an additional brain-MRI within 48 h after hospital admission. The included patients will be followed for two years to identify recurrent ischemic strokes and to evaluate 90-day clinical outcome.

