### Statistical analysis

#### Ischemia detection

##### Sample size

Over 30,000 people suffer from an ischemic stroke in the Netherlands each year.^31^ About 30% of them will have an intracranial large artery occlusion, and 70% will have a minor stroke or TIA. As a result, 500 of the 720 subjects are possible candidates for small volume infarct detection. Assuming that at least half of the 500 patients will give informed consent for the extra follow-up MRI and do not have contra-indications for undergoing MRI, we should have 250 potential patients for the part of the study that concerns small volume stroke detection. Based on the historical cohort (Dutch Acute Stroke Study: 2009–2013, METC number 08–373), we expect to improve the sensitivity of CTP for small volume stroke detection from 0.45 to at least 0.75, which approaches the sensitivity of MRI (0.88–1.00).^32^ With a minimal acceptable lower 95% confidence level of 0.6 for the increased sensitivity, we will need about 107 MRI subjects.^33^ We expect that about 60% of patients with suspected stroke, and no large artery occlusion on admission will have an infarct on follow-up imaging.^34^ This means that we need to include at least 178 patients for the MRI part of this study.

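### The figure 720 is used both as the number of patients approached and as the number enrolled, so planned enrolment is either about 648 or 720

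*Protocol article*

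**What the plan says.** All places are in the protocol article.

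- **Statistical analysis, Recurrent stroke prediction, Sample size.** The model is limited to six predictors ("a prediction model containing a maximum of six predictors will be developed for recurrent stroke"), and the event requirement follows from that: "at least 60 patients with a recurrent stroke are needed according to statistical guidelines". The assumed recurrence is given as "Ischemic stroke is estimated to recur in approximately 10% of the included patients". After loss to follow-up the text reads "When accounting for a loss to follow-up rate of 10%, the required sample size will be approximately 650". After 90% participation it reads "Thus, a minimum of 720 patients need to be asked for study participation". The paragraph closes by saying that at least 720 patients with suspected ischemic stroke will present to the three centers in 36 months.
- **Study design.** "We will include 720 patients with suspected AIS".
- **Statistical analysis, Ischemia detection, Sample size.** "As a result, 500 of the 720 subjects are possible candidates for small volume infarct detection". The text then assumes that at least half of these 500 consent to the extra MRI and have no contraindication, which gives 250. It expects about 60% to have an infarct, and requires 107 patients with an infarct, hence 178 with MRI.

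**The concern.** In the recurrence paragraph, 720 is the count before refusals. In Study design it is the count after refusals. In the MRI paragraph it must also be the count after refusals, because a separate MRI consent step is applied to it afterwards and no step for refusing the main study appears. With 90% participation these two counts differ by 72 patients when 720 is the number approached (720 − 648), or by 80 when 720 is the number enrolled (800 − 720).

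The enrolment target and the expected number of recurrences both depend on which meaning applies. The 60 recurrences are the only justification this paragraph gives for six predictors. One meaning puts the expected count slightly below 60 and the other puts it above. A reader cannot tell from the article whether recruitment is complete at about 648 or at 720 enrolled.

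**Working it through.** **Inputs, all from the article.** Events needed: 60 for six predictors, which is 10 per predictor. Recurrence: about 10%. Loss to follow-up: 10%. Participation: 90%. For the MRI part: 70% without large artery occlusion, half with MRI, 60% with an infarct; required 178 with MRI and 107 with an infarct.

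**1. The article's own chain.**
- Followed: 60 / 0.10 = 600.
- Enrolled: 600 / 0.90 = 667. Multiplying instead, 600 × 1.10 = 660. Stated: approximately 650.
- Approached, from the stated 650: 650 / 0.90 = 722. Stated: 720.
- Approached, without intermediate rounding: 600 / (0.90 × 0.90) = 600 / 0.81 = 741.

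The stated 650 lies 2.6% below 667 as a share of 650 (17 / 650), or 1.5% below 660 (10 / 650). The stated 720 lies 2.9% below 741 as a share of 720 (21 / 720). The step from 650 to 720 confirms that 720 here is the number approached.

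**2. The two meanings carried forward.**

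| Quantity | 720 approached | 720 enrolled |
|---|---|---|
| Approached | 720 | 720 / 0.90 = 800 |
| Enrolled | 720 × 0.90 = 648 | 720 |
| Followed | 648 × 0.90 = 583 | 720 × 0.90 = 648 |
| Expected recurrences at 10% | 58.3 | 64.8 |
| Per predictor, six predictors | 58.3 / 6 = 9.7 | 64.8 / 6 = 10.8 |

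**3. The MRI projection.**
- As written: 0.70 × 720 = 504, stated as 500; half is 250; 0.60 × 250 = 150 with an infarct.
- From 648 enrolled: 0.70 × 648 = 454; half is 227; 0.60 × 227 = 136 with an infarct.

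Both versions exceed the required 178 with MRI and 107 with an infarct.

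**The case against.** The strongest reply is that this is a rough planning calculation, labelled as such. Recurrence and sample size are both given as approximate, and the stated figures lie within 3% of the exact ones. On the less favourable reading the shortfall is 60 − 58.3 = 1.7 expected events. A recurrence rate of 60 / 583 = 10.3%, which still counts as about 10%, would remove it. The 720 is also worded as a floor, so more patients may be approached. All of this stands, and it limits the size of the point. It does not settle which count 720 is.

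A reader might infer more, and the documents do not support it:

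- **That the sample size does not reproduce.** It does, within rounding. What remains is that figures supporting stated minima were rounded down, and that even the more lenient inflation (660) lies above 650.
- **That the 60 recurrences will not be reached.** With 720 enrolled, 64.8 are expected. With 720 approached, the expectation is 58.3. The binomial probability of at least 60 is then 0.43, but with 600 followed, the exact requirement, it is only 0.52. A value near one half is what any plan gives when its expected count equals its target, and the article claims no higher assurance.
- **That the 10% rate contradicts the Background.** The Background says "The two-year recurrence rate has been estimated to be 12% in patients with AIS". The sample-size paragraph speaks of the included patients, who also comprise patients with transient ischemic attack. The populations are described differently, and the lower rate is the cautious one for planning. At 12%, 583 followed would give 70 recurrences.
- **That the model must be cut to five predictors.** A difference of 0.3 events per predictor does not justify that.

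**Conclusion.** The article is wrong as written on one matter: 720 cannot be both the number approached and the number enrolled when participation is 90%. Planned enrolment is about 648 on one reading and 720 on the other, and the expected recurrences are 58 or 65. The rounding down from 667 and 741 is a minor companion point.

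The consequence is modest. On the less favourable reading the expected count falls 1.7 below the stated minimum, and the MRI part keeps a margin of 227 against 178 and 136 against 107. The conclusion rests on the article's own rates: 10% recurrence among those followed, 10% loss and 90% participation. The contradiction itself needs only that participation is below 100%. It should be corrected because a sample size is a figure the study relies on, but it threatens no objective.

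**What to change.** Give 720 one meaning in Study design and in both sample-size paragraphs, and write out the chain from approached to expected events.

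- **If 720 is the number approached:** state about 648 enrolled, 583 followed and 58 expected recurrences, about 9.7 per predictor for six predictors. Change Study design to match. Restate the MRI projection as about 454 candidates, 227 with MRI and 136 with an infarct, still above 178 and 107.
- **If 720 is the number enrolled:** state that about 800 are to be approached and that 648 followed and 65 recurrences are expected. The MRI projection can stay. The closing remark on patient flow should then refer to about 800, because a flow of at least 720 shows no margin for refusals.

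On either choice, give the unrounded 667 and 741 as the exact requirement, or say that the figures used are rounded down.

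The cost is a text correction. No extra patients are needed if the figures are restated; the only downside, on the first choice, is slightly less favourable stated figures.

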##### Candidate predictors

In this study, clinical and imaging predictors of recurrent stroke will be analyzed. Previously identified clinical predictors include cardiovascular risk factors such as higher age, prior stroke, prior myocardial infarction, atrial fibrillation, hypertension, diabetes mellitus, and hyperlipidemia.^25^ Predictors, that can be determined on imaging modalities, include previous cerebral infarcts on NCCT, ASPECTS on CTP, and CTA findings such as occlusion or stenosis, collateral filling in the occluded area, carotid plaque characteristics, and presence of a cardioembolic source. Stroke subtype (TOAST) classification is based on both clinical and imaging data.

##### Model derivation

Complete case analysis will be performed as we expect only few missing values. A multivariable model containing all candidate predictors will be developed. The best predictive variables will be selected with backward selection. Akaike’s information criterion will be used to determine the best model fit. Hazard ratios and 95% confidence intervals will be calculated with Cox proportional hazards models. The proportionality hazards assumption will be checked by visual inspection of the Schoenfeld residual plots. The performance of the final model will be evaluated with measures of discrimination and calibration. Discrimination will be assessed with ROC curves and c-statistics. Calibration will be assessed with calibration plots.

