## Abstract

**Background:**

Computed tomography is the most frequently used imaging modality in acute stroke imaging protocols. Detection of small volume infarcts in the brain and cardioembolic sources of stroke is difficult with current computed tomography protocols. Furthermore, the role of computed tomography findings to predict recurrent ischemic stroke is unclear. With ENCLOSE, we aim to improve (1) the detection of small volume infarcts with thin slice computed tomography perfusion (CTP) images and thromboembolic source with cardiac computed tomography techniques in the acute stage of ischemic stroke and (2) prediction of recurrent ischemic stroke with computed tomography-derived predictors.

Methods/design: ENCLOSE is a prospective multicenter observational cohort study, which will be conducted in three Dutch stroke centers (ClinicalTrials.gov Identifier: NCT04019483). Patients (≥18 years) with suspected acute ischemic stroke who undergo computed tomography imaging within 9 h after symptom onset are eligible. Computed tomography imaging includes non-contrast CT, CTP, and computed tomography angiography (CTA) from base of the heart to the top of the brain. Dual-energy CT data will be acquired when possible, and thin-slice CTP reconstructions will be obtained in addition to standard 5 mm CTP data. CTP data will be processed with commercially available software and locally developed model-based methods. The post-processed thin-slice CTP images will be compared to the standard CTP images and to magnetic resonance diffusion-weighted imaging performed within 48 h after admission. Detection of cardioembolic sources of stroke will be evaluated on the CTA images. Recurrence will be evaluated 90 days and two years after the index event. The added value of imaging findings to prognostic models for recurrent ischemic stroke will be evaluated.

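### The stated prediction analysis yields one selected model and no clinical-only comparator, so it does not estimate the added value of CT predictors that is the study's second goal

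*Protocol article*

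**What the plan says.** The protocol article states the aim twice. Background: "The second goal of ENCLOSE is to prospectively evaluate the added value of CT-derived predictors for predicting recurrent ischemic stroke". Abstract: "The added value of imaging findings to prognostic models for recurrent ischemic stroke will be evaluated". The Discussion gives the reason: existing clinical models discriminate poorly over the long term, and adding imaging might improve them.

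Candidate predictors lists both kinds of variable. The clinical ones are "higher age, prior stroke, prior myocardial infarction, atrial fibrillation, hypertension, diabetes mellitus, and hyperlipidemia". The imaging ones are earlier infarcts on non-contrast CT, ASPECTS on CTP, and several CTA findings, including carotid plaque and a cardioembolic source. The section ends with: "Stroke subtype (TOAST) classification is based on both clinical and imaging data".

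Model derivation then sets the analysis. "A multivariable model containing all candidate predictors will be developed". "The best predictive variables will be selected with backward selection". Akaike's criterion decides the best fit, and Cox models supply the hazard ratios. On performance: "The performance of the final model will be evaluated with measures of discrimination and calibration", and "Discrimination will be assessed with ROC curves and c-statistics".

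**The concern.** Added value is a difference: how well recurrence is predicted with the CT findings, minus how well it is predicted without them, in the same patients. The procedure described produces only the first of these quantities. Clinical and imaging candidates enter together, either kind may be dropped, and performance is reported once, for the model that remains.

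If the section is followed as it stands, the study ends with a prediction model and some adjusted hazard ratios, but without a direct answer to its second goal. A clinical comparator could be added after the data are seen. Its composition would then be open to choice by result, and the apparent CT gain depends heavily on how strong or weak that comparator is.

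**Working it through.** **1. The plan's own figures.** The sample size for this part is not in dispute.
- Events: the plan asks for 60 for at most 6 predictors, which implies 60 / 6 = 10 events per predictor.
- Patients: 60 / 0.10 = 600.
- With 10% loss to follow-up: 600 / 0.90 = 667, or 600 × 1.10 = 660. The plan says approximately 650.
- With 90% participation: 650 / 0.90 = 722. The plan says 720.

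The figures reproduce to within about 3%. They size the development of one model of up to six predictors. No comparison of two models enters them.

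**2. Goal and analysis side by side.**

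| Needed to measure added value | In Model derivation |
|---|---|
| Clinical-only model | Not described |
| Clinical predictors held fixed when CT is added | No; all candidates are subject to backward selection |
| Test of the CT predictors as a block | Not described |
| Difference in c-statistic between two models | Not described; c-statistics are for the final model |

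**3. Can the comparator be recovered from the final model?** Not reliably. The clinical variables left after selection are those that survived with CT terms present. A clinical variable correlated with a CT term may have been dropped in its favour. Deleting the CT terms afterwards would leave a weakened clinical set, and the difference could then overstate what CT adds.

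**4. Does one pooled c-statistic determine the increment?** This was checked by simulation. The inputs below are assumptions, except that the event rate was set near the plan's 10%.
- 1,000,000 subjects per scenario and a binary outcome.
- Linear predictor = clinical part + imaging part, independent and normal, with total SD 0.85.
- Clinical SD = 0.85 × √(1 − s) and imaging SD = 0.85 × √s, where s is the imaging share of the variance.
- Event probability = 1 / (1 + exp(−(LP − 2.5))), giving 9.7% to 9.8% events.

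| Imaging share s | Pooled c | Clinical-only c | Increment |
|---|---|---|---|
| 0% | 0.719 | 0.719 | 0.000 |
| 10% | 0.719 | 0.707 | 0.011 |
| 30% | 0.719 | 0.684 | 0.035 |
| 50% | 0.720 | 0.657 | 0.063 |

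(Increments were computed before rounding.) The pooled value barely moves while the increment runs from nothing to 0.063. The final model's c-statistic alone therefore does not identify added value.

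**The case against.** The strongest reply is that the article is a condensed account. Its Abstract commits to evaluating added value, Model derivation nowhere rules out a base model, and the full protocol or analysis plan may specify one. That possibility stands. It does not remove the point, because the section does more than stay silent. It names the starting model, the selection method, the criterion and the performance measures, and that set does not deliver the stated goal.

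A second reply is that the procedure does say something about incremental information. A CT term kept under Akaike's criterion has improved penalised fit given the other retained variables, and its hazard ratio is adjusted for them. The all-candidate starting model is also the larger half of a nested pair. This too stands, so a reader should not infer that the analysis says nothing at all about CT predictors. It shows conditional association among selected variables, not the gain in prediction.

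Two stronger readings are tempting and are not supported:
- **That TOAST absorbs the CT contribution and biases it towards none.** TOAST appears in the candidate section but is not expressly called a candidate. No passage says it is assigned from the admission CTA or cardiac CTA, and no calculation shows the direction or size of any bias. Removing it is also debatable: Background calls aetiology an important predictor of recurrence, so a base model without it could be too weak and flatter CT.
- **That the final model will be judged against the published c-statistics of at most 0.7, with overfitting creating a false gain.** The Discussion gives that figure as background and proposes no such comparison. Overfitting is a separate matter from the missing comparator.

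**Conclusion.** The concern holds as a mismatch between a stated goal and a stated analysis. Followed as written, Model derivation yields adjusted hazard ratios for any retained CT predictors. It gives no clinical-only comparator in the same patients, no fixed clinical base from which to reconstruct one, and therefore no estimate of the gain in prediction.

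It affects one of the study's two goals. It does not affect the ischaemia detection part or the data collected.

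The range of 0.000 to 0.063 is an illustration of non-identifiability, not a forecast. It rests on the assumed SD of 0.85, imaging shares of 0% to 50%, independence of the two parts and a binary outcome in place of time to event. The core conclusion rests on the text alone. It would change only if the unseen full protocol or analysis plan already prespecifies the nested comparison.

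**What to change.** In Model derivation, prespecify two models fitted in the same patients:
1. A clinical base model, either with fixed predictors and no selection, or with the linear predictor of an existing clinical model as a single term.
2. The same model plus a fixed block of CT predictors.

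Together they should stay within the stated limit of six predictors. With an existing linear predictor as one term, 6 − 1 = 5 places remain for CT. Since complete-case analysis is planned, both models should use the patients complete for the larger one.

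Report the likelihood-ratio test for the CT block and the difference in optimism-corrected c-statistic with a bootstrap interval. The backward-selected model can remain as a secondary product.

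For TOAST, state in advance which block it belongs to, and show the increment with and without it as a sensitivity analysis rather than deleting it. State also how it counts towards the limit: entered as five categories (an assumption) it would use four coefficients, leaving 6 − 4 = 2.

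The cost is a little more analysis work and a choice of predictors made before outcome data are examined. No new data, recruitment or procedures are needed.

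### Hazard ratios with ordinary 95% CIs appear to come from the AIC-selected Cox model with no allowance for selection, so retained CT findings will look better established than they are

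*Protocol article*

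**What the plan says.** The protocol article, Statistical analysis, Recurrent stroke prediction, Model derivation, sets out these steps in order:

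1. "A multivariable model containing all candidate predictors will be developed".
2. "The best predictive variables will be selected with backward selection".
3. "Akaike’s information criterion will be used to determine the best model fit".
4. "Hazard ratios and 95% confidence intervals will be calculated with Cox proportional hazards models".
5. Proportional hazards are checked, and the final model is assessed for discrimination and calibration.

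Step 4 does not say which Cox model supplies the hazard ratios. No shrinkage, bootstrap of the selection or full-model reporting is mentioned. No significance test is attached to the hazard ratios; the 0.05 threshold under Diagnostic value belongs to the CTP comparison.

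The Sample size paragraph for this part says "a prediction model containing a maximum of six predictors will be developed for recurrent stroke" and "at least 60 patients with a recurrent stroke are needed according to statistical guidelines". Candidate predictors names seven clinical factors, stroke subtype, and imaging findings that "include previous cerebral infarcts on NCCT, ASPECTS on CTP, and CTA findings such as occlusion or stenosis, collateral filling in the occluded area", plus carotid plaque and cardioembolic source. That is about 14 in all. Background gives the state of knowledge: "CT-derived predictors have been identified as prognostic for clinical outcome after AIS, but not yet for recurrences".

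**The concern.** A 95% CI from a Cox model has its stated coverage when the model was fixed before the data were seen. Here the natural reading is that the model is whatever AIC leaves, chosen on the same events that then give the estimates. A term appears in the final table only because its estimate was already large relative to its standard error. Given that, its hazard ratio is pushed away from 1 and its ordinary interval is too narrow.

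Selection is heavy: about 14 candidates against a ceiling of six. Because the article says CT findings are not yet established for recurrence, a table of retained findings with hazard ratios and CIs could be taken as first evidence of which ones matter. The intervals would then be asked a question they do not answer.

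**Working it through.** **The plan's own figure.** 60 events for six predictors is 60/6 = 10 events per predictor. At 10% recurrence, 60/0.10 = 600 patients. With 10% loss, 600/0.90 = 667 (or 600 × 1.10 = 660), both within 3% of the stated 650. At 90% participation, 650/0.90 = 722, against the stated 720. The size reproduces. Expected events are 650 × 0.90 × 0.10 = 58.5, so about 60.

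**Closed form for a retained null term.** Dropping a one-parameter term lowers AIC if its likelihood-ratio chi-square is below 2. A null term is therefore kept with probability

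P(chi-square with 1 df > 2) = P(|Z| > √2) = 0.157.

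Taking the Wald and likelihood-ratio statistics as equal, a CI that excludes 1 (|Z| > 1.96) implies retention, so

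P(CI excludes 1 | null and retained) = 0.05/0.157 = 0.318.

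Coverage among retained null terms is thus about 68%, not 95%. For terms with several parameters, the same ratio for the joint 5% test is 37% (2 df), 45% (3 df) and 55% (4 df).

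**Simulation 1.** Assumptions: 585 followed patients, about 60 recurrences, seven clinical candidates with modest effects, seven CT candidates with none.

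- At least one null CT finding was retained in 67% of 400 runs (75% if nothing predicts).
- In 600 runs there were 600 × 7 = 4,200 null CT terms, of which 717 were retained. Of these, 30.7% had a CI excluding 1.
- In the full model the rate was 4.9% per null term.

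**Simulation 2.** Assumptions: 650 patients, about 60-65 events, 14 candidates, 400 runs per setting.

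| Setting | Null terms retained | CI excludes 1, given retained | CI excludes 1, per null candidate | Full model, per null candidate |
|---|---|---|---|---|
| No true predictors, continuous | 0.168 | 0.306 | 0.051 | 0.052 |
| Five true, continuous, correlation 0.2 | 0.168 | 0.354 | 0.059 | 0.058 |
| Five true, binary, correlation 0.2 | 0.174 | 0.338 | 0.059 | 0.053 |
| As above, cap of six enforced | 0.125 | 0.416 | 0.052 | 0.050 |

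**False exclusions per study (simulation 1).** After selection: 717 × 0.307 = 220, and 220/600 = 0.37 per study, or 220/4,200 = 5.2% per null candidate. Full model: 7 × 0.049 = 0.34 per study. The two are nearly equal. Selection mainly removes the unremarkable null terms from view.

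**Size of the exaggeration.** For a binary finding with an assumed 30% prevalence and 60 events, the standard error of the log hazard ratio is about 1/√(60 × 0.3 × 0.7) = 0.28. Retention needs |log HR| > √2 × 0.28 = 0.40, so a null finding in the final table shows a hazard ratio of at least about 1.5, or its inverse. Simulation 1 gave a median of about 1.7.

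**Cost of the full model.** 60/14 = 4.3 events per candidate, before counting the extra parameters of the stroke-subtype classification.

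**The case against.** **The source model is not stated.** This stands as a limit. Model derivation speaks of Cox models in the plural and ties only discrimination and calibration to the final model. If the full model supplies the hazard ratios, the problem disappears. The order of the text points the other way, and one clause would settle it. The article condenses a fuller plan that may already do so.

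**Setting 32% against 5% compares unlike things.** This also stands. A reader might infer that about a third of null CT findings will be declared predictive, or that selection multiplies false findings sixfold. Neither follows: the 32% holds only among retained null terms, and per null candidate the rate stays at about 5-6% with or without selection. The conditional rate still matters, because retained terms are what a final-model table shows.

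**The aim is prediction.** The article judges the model by c-statistics, ROC curves and calibration, and ties no decision to these CIs. A reader might infer that the plan will declare CT findings prognostic because their CIs exclude 1; it does not say so. The harm is therefore one of interpretation. It remains, because a CI printed beside a hazard ratio invites that reading.

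**The full model is fragile.** With about 4 events per candidate against the 10 planned, its estimates will be less stable. Collateral filling also has no obvious value in patients without an occlusion, which sits badly with complete-case analysis. This must be admitted in any fix. It also means that forbidding CIs for the reduced model would be a preference; labelling or bootstrapping them is enough.

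**Conclusion.** The concern holds in a limited form. On the natural reading of Model derivation, ordinary 95% CIs for terms retained by AIC are too narrow and the hazard ratios lie too far from 1. For a retained one-parameter null finding, the CI excludes 1 about 32% of the time. That figure needs only the AIC rule and large-sample normality. Simulation gives 31-35%, and about 42% in the setting where the six-predictor cap was enforced.

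The error is in how retained terms are read, not in how many false findings the study produces. The 67% chance of retaining some null CT finding and the median hazard ratio of about 1.7 depend on assumptions the article does not give: the count of 14 candidates, null CT effects, effect sizes and prevalence. The assessment of the model by discrimination and calibration is not the subject of this point.

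**What to change.** In Model derivation:

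- Name the model that supplies the hazard ratios.
- Report hazard ratios and 95% CIs for all candidates from the pre-selection model, which the plan already fits. State that they will be wide and less stable, at about 4 events per candidate against the 10 behind the sample size.
- Present the AIC-reduced model as the prediction tool. Either label its coefficients and any CIs as post-selection, or take the intervals from a bootstrap that repeats the whole selection.
- State that neither retention nor a post-selection CI excluding 1 will be treated as evidence that a CT finding predicts recurrence.

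The cost is a few sentences and one more table, plus computing time if the bootstrap is chosen. No patients, data or study procedures change. The price is wider intervals and a full model that is thin for the number of events, which the report should say openly.
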